### Sample size calculation

2.6.

The participants will be randomly divided into functional training group (control group) and hip-knee-ankle Tuina group (intervention group), the allocation ratio of the two groups is 1:1. Sample size calculation is based on the Y-Balance Test (the primary outcome), the sample size formula for comparison of means between two groups in a randomized controlled trial is used to perform the sample size calculation. With the test levels set at *α* = 0.05 (2-sided), *β* = 0.1, according to the relevant literature at home and abroad (31, 35), the maximum acceptable right/left reach distance difference was 4 cm. The standard deviation of the comprehensive score of Y-Balance test in the pre-experimental observation was 4.95. It is substituted into the sample size calculation formula, *n* = 32.15. Considering a 10% dropout rate, and take the integer *n* = 36, so we will include 36 participants for each group, the total number of participants is 72.

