##### Y-balance test (YBT)

2.5.1.1.

The first primary outcome measure is the stability and balance of lower limbs evaluated by the Y-Balance Test (YBT). Y-Balance Test is a clinical instrument base on star excursion balance test (SEBT) which is commonly used for assesses dynamic stability and neuromuscular control of the lower extremity, and studies have proofed its reliability (30). The YBT will be assessed before and after Tuina treatment.

Before the YBT, participants will be instructed to learn the correct stretch technique and allowed four practice trials in each direction, with three consecutive test trials in each direction during testing. The order of the directions is random. Composite scores and two-sided differences will be calculated at the end of the test. The calculation formula is shown below. If the composite score is less than 95%, it indicates poor joint stability, and there may be a high risk of injury to the support leg, a lower score indicates a higher risk of injury. If bilateral difference is greater than 5%, it suggests a large difference in strength or balance between the left and right support legs, a higher difference indicates a higher risk. Studies have shown that patients with an anterior right/left reach distance difference greater than 4 cm would be 2.5 times more likely to sustain a lower extremity injury (31).$$\mathrm{Composite}\;\mathrm{score}=\frac{a+b+c}{L\times 3}\times 100\text{\%}$$$$\mathrm{Two}\text{-}\mathrm{sided}\;\mathrm{differences}=\frac{\left(a1+b1+c1)-(a2+b2+c2\right)}{(a1+b1+c1+a2+b2+c2)/2}\times 100\text{\%}$$Notes: *a*1, *b*1, *c*1, *a*2, *b*2 and *c*2 represent the farthest distance of the left/right foot extended in the three directions respectively. *L* represents the length of the leg.

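### The sample size pairs a 4 cm between-leg injury cut-off with the SD of the Y-Balance composite score, so the stated 90% power is unsupported as written

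*Protocol article*

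**What the plan says.** Section 2.6 (Sample size calculation) identifies the outcome only by the name of the test: "Sample size calculation is based on the Y-Balance Test (the primary outcome"). It states the method, "the sample size formula for comparison of means between two groups in a randomized controlled trial is used", and the error rates, "With the test levels set at *α* = 0.05 (2-sided), *β* = 0.1". Two inputs follow in adjoining sentences, a difference and a measure of variability: "the maximum acceptable right/left reach distance difference was 4 cm. The standard deviation of the comprehensive score of Y-Balance test", the latter put at 4.95 from pilot data. The result is reported as "It is substituted into the sample size calculation formula, *n* = 32.15". An allowance of 10% for dropout then brings this to 36 per group, 72 in all.

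Section 2.5.1.1 (Y-balance test) shows what these quantities are. The composite score is the sum of the three reach distances divided by three times the leg length, times 100%. The two-sided difference is also a percentage: the gap between the legs' three-direction sums, relative to their average. These are the two scores that the section says will be calculated. The 4 cm figure appears there as a risk marker from a cited study: "patients with an anterior right/left reach distance difference greater than 4 cm would be 2.5 times more likely to sustain a lower extremity injury".

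**The concern.** A two-means sample size formula needs the difference to be detected between the arms and the standard deviation of the same variable. Here the two inputs differ in three ways.

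- **Unit.** One is in centimetres. The other is the SD of a score that its formula makes a percentage of leg length.
- **Variable.** One compares a person's two legs. The other describes a composite of three directions for one leg.
- **Meaning.** The 4 cm marks how much asymmetry is acceptable within a person. It does not say how much better the Tuina arm should do than the control arm.

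This is the only justification of sample size in the article, and section 2.2 presents the trial as one that will confirm efficacy. If the result is null, readers will take it as coming from a trial with 90% power. They would not know which effect, on which Y-Balance score, that power refers to.

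**Working it through.** **Inputs**

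| Quantity | Value | Source |
|---|---|---|
| Two-sided alpha | 0.05 | section 2.6 |
| Beta | 0.1 (power 90%) | section 2.6 |
| Difference used | 4 cm, right/left reach | section 2.6 |
| SD used | 4.95, comprehensive score, no unit printed | section 2.6 |
| Composite score | (a+b+c)/(3L) × 100% | section 2.5.1.1 |
| Dropout | 10% | section 2.6 |

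**Step 1: reproduce the plan's figure.** For two means with 1:1 allocation, n per group = 2 × [SD × (z for alpha + z for beta) / difference]².

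- With z rounded to 1.96 and 1.28: 2 × (4.95 × 3.24 / 4)² = 32.15, the printed value to two decimals.
- With unrounded z: 32.18.
- A one-sided test at 90% power gives 26.2, and a two-sided test at 80% power gives 24.0. Neither matches.
- Dropout: 32.15 / 0.9 = 35.7, rounded up to 36. This agrees with the plan.

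The arithmetic is correct. It also shows that the 4 cm and the composite-score SD were put into one ratio, 4/4.95 = 0.81.

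**Step 2: compare the scales.** Neither score that section 2.5.1.1 plans to calculate is in centimetres. For the composite, the article gives an SD but no between-arm difference. For the two-sided difference, it gives neither an SD nor a between-arm difference; the 5% quoted there is again a risk cut-off. So the documents do not determine a single corrected n.

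**Step 3: what 36 per arm delivers if the composite is kept.** The SD is taken as 4.95 percentage points and alpha as 0.05 two-sided. The between-arm difference is an assumption in every row. The noncentrality is difference / (SD × √(2/n)).

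| Assumed difference (points) | n per arm | Noncentrality | Power | Method |
|---|---|---|---|---|
| 4 | 36 | 4 / 1.167 = 3.43 | about 92% | t-test |
| 4 | 32 | 4 / 1.2375 = 3.23 | about 89% | t-test |
| 3.6 | 36 | 3.6 / 1.167 = 3.09 | about 86% | t-test |
| 5 | 32 | 5 / 1.2375 = 4.04 | about 98% | normal approximation |
| 3 | 32 | 3 / 1.2375 = 2.42 | about 68% | normal approximation |
| 2 | 32 | 2 / 1.2375 = 1.62 | about 37% | normal approximation |

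The 32 is 36 × 0.9 = 32.4, rounded down, and corresponds to an analysis of completers. The 3.6-point row reflects section 2.9, which plans an intention-to-treat analysis with last observation carried forward. All 36 per arm are then analysed. If 10% in each arm carry their baseline value forward, a 4-point effect shrinks to 0.9 × 4 = 3.6 (SD held at 4.95).

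**Step 4: n needed for 90% power on the same assumptions, before dropout.** At 2, 3, 4 and 5 points: 129, 58, 33 and 21 per group (normal approximation). The planned size is generous or short depending on a target that the article does not state.

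**The case against.** The best defence is that the result is serviceable. If the 4 is read as 4 percentage points on the composite, the planned size gives close to 90% power for a score that the trial will measure. This stands as arithmetic. However, the article never states a 4-point target between arms and gives no reason for one. The figure fits only because the numeral from the centimetre threshold is kept and its unit changed.

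A second defence is that 4.95 carries no unit, that section 2.6 says comprehensive score where section 2.5.1.1 says composite score, and that the word anterior appears only in section 2.5.1.1. Section 2.6 also cites a second source for the 4 cm, which cannot be seen here. These are fair limits. The percentage scale is an inference, but a strong one, since section 2.5.1.1 defines only one composite. Whatever the direction of reach, a right/left distance in centimetres is not that composite.

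Two stronger readings are tempting, and the documents support neither. A reader might infer that the trial is badly underpowered, by converting 4 cm in one direction into a small shift in the composite. That conversion needs leg lengths that the article does not give, and it treats an asymmetry cut-off as a treatment effect, which is the very step in dispute. A reader might also infer that rounding 32.15 up to 33 first would require 37 per arm. Dividing 32.15 by 0.9 and rounding up to 36 is a valid route.

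**Conclusion.** Wrong as written. The difference and the SD in section 2.6 come from different quantities on different scales, and a between-leg cut-off is not a between-arm effect. The stated 90% power is therefore unsupported. The calculation itself is accurate; the fault lies in what was entered.

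The finding does not show that 72 participants are too few. On the composite, power for the planned size runs from about 37% at 2 points to about 98% at 5 points (32 per arm, normal approximation), and nothing in the article says where in that range the intended effect lies. These figures rest on reading 4.95 as percentage points and on the differences assumed. The identity of the inputs rests only on the article's text and on the exact match to 32.15.

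**What to change.** Rewrite the paragraph in section 2.6 on one scale:

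1. Name the Y-Balance variable that is primary: the composite score or the two-sided difference.
2. Remove the 4 cm cut-off as the source of the target difference.
3. Give a between-group difference on the scale of that variable, with its justification, and an SD of the same variable. If the two-sided difference is chosen, an SD for that score is needed; 4.95 does not serve.
4. Restate the power that 36 per arm delivers, and say which analysis set it refers to.

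If the composite with SD 4.95 is kept, report power as conditional on the assumed difference. For 4 points (t-test) it is about 92% with 36 per arm analysed and about 89% with 32 evaluable. It is about 86% under intention-to-treat with carried-forward values, if 10% retain baseline and dilute the effect to 3.6 points. State also that power falls for smaller differences, as in the table above. Four points should be the target only if it can be justified in its own right.

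The cost is one paragraph of text. The stated power becomes conditional and may look less favourable; N can stay at 72 and no extra patients are needed.

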### Randomization, allocation, and blinding

2.7.

We will use Statistical Package for the Social Sciences (SPSS) Ver.25.0 (IBM Inc, New York, USA) and manual assistance to complete randomization, the method is shown below.

Before the study, a randomization specialist, who will not join other part of this trial, will be set up, and the specialist will use SPSS Ver.25.0 to generate a set of random numbers according to the numbers 1–72. After that, the numbers will be sorted according to the order of random number from small to large, 72 numbers will be randomly divided into the intervention group and the control group, and the numbers and corresponding groups will be sent to the researchers. When the appropriate participants are recruited, the researchers will enter the form and number it according to the order of enrollment, and determined the group of the current case according to the grouping generated by the randomization specialist. The lists of the two groups are sorted into tables and sent to the doctor, who are informed of the treatment plan for each group in advance, in order to reduce unnecessary communication between researchers and randomization specialist in the grouping process, and avoid the influence of researchers' subjective will on the grouping as much as possible. The participants and the doctor will not be blinded because of specialization of Tuina. However, the data analysis and efficacy assessment will be performed by the research assistant, who will not join other part of this trial, and blinded in order to decrease analysis bias.

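### The researchers who enter and number participants are sent the whole allocation list, so the next assignment can be known and allocation is not concealed

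*Protocol article*

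**What the plan says.** The procedure is in section 2.7 (Randomization, allocation, and blinding) of the protocol article. In order:

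1. Before the study, "a randomization specialist, who will not join other part of this trial, will be set up".
2. The specialist generates random numbers in SPSS and sorts by them, and "72 numbers will be randomly divided into the intervention group and the control group".
3. Then "the numbers and corresponding groups will be sent to the researchers".
4. Once suitable participants have been recruited, "the researchers will enter the form and number it according to the order of enrollment", and they "determined the group of the current case according to the grouping generated by the randomization specialist".
5. "The lists of the two groups are sorted into tables and sent to the doctor". The doctor is also told beforehand what treatment each group receives.

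The section gives two reasons for this arrangement: less contact between researchers and specialist while participants are being grouped, and to "avoid the influence of researchers' subjective will on the grouping as much as possible". Participants and the doctor are not blinded. Efficacy assessment and data analysis are done by a blinded research assistant.

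**The concern.** Random assignment protects a comparison only if the person who decides whether and when to enter a participant cannot foresee the assignment. Here the order of enrolment determines the number, the number determines the group, and the people who assign the number have the key. If the next group is known, a borderline candidate can be entered now, delayed or passed over, and the arms can come to differ in prognosis.

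There is room for this. Some entry criteria in sections 2.3.1 and 2.3.2 call for judgement, such as whether a sprain was severe, what counts as an episode of instability, and whether a patient understands the scales. What is at stake is the validity of the between-group comparison in a trial that section 2.2 describes as meant to confirm efficacy.

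**Working it through.** **1. The steps of section 2.7 side by side**

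| Step | Who | What they hold or do |
|---|---|---|
| Generate all 72 assignments before the study | Specialist | Full list |
| Receive numbers with groups | Researchers | Full list |
| Number each case by enrolment order | Researchers | Fixes which line of the list applies |
| Read off the group | Researchers | From the specialist's grouping |
| Receive group tables | Doctor | Timing of receipt not stated |

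If 14 participants are in, the next is number 15, and the group of number 15 is on the list the researchers already have. This holds for each of the 72 positions. The section describes no sealed envelope, no release on request, and no separation between the person who enters participants and the person who holds the list.

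**2. How predictable the next assignment is**

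- List held by the researchers: 72 of 72 assignments can be known, or 100%.
- Concealed list with 36 per arm, guessing without knowledge of past assignments: 50% correct.
- Same concealed list, knowing all past assignments and always guessing the arm with more places left: about 57% correct (40,000 simulated lists).

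**3. The plan's own figures, for the group size used below**

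Section 2.6 uses a two-sided α of 0.05, β of 0.1, a difference of 4, an SD of 4.95 and 10% dropout.

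n = 2 × (4.95 × (1.96 + 1.28) / 4)² = 32.15, as stated. Then 32.15 / 0.9 = 35.7, so 36 per group and 72 in total. The figures are reproduced, and the concealment point does not change them.

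**4. What a given amount of steering would do (assumed shifts)**

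Suppose there is no true treatment effect, but steering makes the arms differ in the outcome by d standard deviations. With 36 per arm the test statistic is shifted by d × √(36/2) = d × 4.243. The false-positive rate of an unadjusted two-sided 5% test (normal approximation) is

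P = 1 − Φ(1.96 − shift) + Φ(−1.96 − shift).

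| Assumed d | Shift in z | Upper tail | Lower tail | P |
|---|---|---|---|---|
| 0 | 0 | 0.025 | 0.025 | 5% |
| 0.1 | 0.424 | 0.062 | 0.009 | about 7% |
| 0.25 | 1.061 | 0.184 | 0.001 | about 19% |
| 0.4 | 1.697 | 0.396 | 0.000 | about 40% |

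None of these values of d comes from the documents. I leave the shift in SD units and do not express it as a share of the planning difference. Section 2.6 gives that difference as a right/left reach distance in cm, while the SD of 4.95 belongs to the Y-Balance composite score.

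**5. Do other safeguards cover this?**

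- The independent specialist ensures that the sequence is random, not that it is hidden.
- Blinded assessment and analysis (section 2.7 and the Discussion) act after allocation. The Discussion names the specialist as protection against detection bias, which is a different bias.
- Section 2.9 foresees covariance analysis if a baseline characteristic needs adjustment. This could reduce bias carried by measured baseline values, but not bias from unmeasured prognosis.

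**The case against.** The best counter-argument is that this is a condensed article. It does not say in what form the list is sent, and the full protocol might provide for sealed assignments. It uses the passive for recruitment and does not say who judges eligibility or obtains consent, so the researchers holding the list might not be the people who decide on entry. Several criteria (CAIT of 27 or less, number of episodes, age) leave little discretion.

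Part of this stands. That the same people recruit, judge eligibility and hold the list is likely but not stated. What is stated is that the researchers receive numbers with groups, assign the number by order of enrolment and determine the group. The wish to reduce contact with the specialist also fits a list that has left the specialist's hands. The article is therefore not silent on concealment: it describes a mechanism that removes it. Countable criteria narrow the room for steering but do not close it.

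Two stronger readings are tempting and are not supported.

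- A reader might infer that the treating doctor, too, has the full list before enrolment. In the text, the advance notice refers to the treatment plan for each group. The timing of the tables is not given, they may list participants already allocated, and the doctor is not said to enrol anyone.
- A reader might infer that steering will happen, or that the error rate is a particular figure. The text shows only that steering is possible.

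**Conclusion.** The point holds for the researchers' list. As section 2.7 is written, those who enter and number participants can know every upcoming assignment, so allocation is not concealed, and the procedure works against its own aim of limiting researchers' influence. Randomisation may then fail to protect the comparison, and no planned analysis reliably restores that protection.

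The size of any bias cannot be derived from the documents. The illustrative rates of about 7%, 19% and 40% rest on assumed shifts of 0.1, 0.25 and 0.4 SD, 36 analysed per arm, no true effect and no baseline adjustment. The conclusion does not depend on them. It should be fixed, because concealment is basic to the design and easy to secure here.

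**What to change.** Amend section 2.7 so that the randomization specialist keeps the list. For each participant, eligibility, consent and the baseline Y-Balance Test, CAIT, FAAM and range-of-motion measurements are recorded and the participant is registered. Only then is that single assignment released, either by message from the specialist or by opening the next of a set of sequentially numbered, opaque, sealed envelopes prepared by the specialist. The doctor is told each assignment only after that point.

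The cost is a short amendment and one contact or one envelope per participant. The specialist's role already exists, and the sample size stays at 72. The small downside is more contact with the specialist, which the present text tries to avoid; envelopes largely remove it.

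If recruitment has begun (the Trial status section gives March 2023 to June 2024), record the date of the change and report it with the results.

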### Data collection and management

2.8.

We will collect the baseline data before the study. The primary and secondary outcomes will be assessed at baseline and 4 weeks (at the end of the intervention). The researcher will collect the data in the case report form (CRF) after obtaining signed consent from the participants. To protect the privacy of the participants, we will use codes and initials instead of their personal information. After data uploading and confirming, only statistician can access to the data.

### Statistical analysis

2.9.

The principle of Intention-To-Treat (ITT) analysis and Per-Protocol (PP) analysis will be followed in the process of statistical analysis. The Last Observation Carried Forward Analysis (LOCF) rule will be applied for missing data in ITT analysis. All the statistical analysis will be performed using SPSS Ver.25.0 with a significance level of 0.05.

First, the different baseline characteristics of the two groups will be described, data will be presented as mean or median with standard deviation or interquartile range for continuous variables and as frequency distributions for categorical variables. Moreover, the histograms, boxes and other representations will also be considered for the graphic analysis of corresponding data. Two-sample *t*-test for quantitative data or Chi-square test for qualitative data will be performed as homogeneity test, and the covariance analysis will also be performed if an adjustment is needed for a baseline characteristic.

Second, the analyses will focus on whether statistically better treatment outcomes could be achieved in the intervention group. *p* Values less than 0.05 were considered statistically significant and tests were 2-sided.

Third, safety analysis will be performed using the Chi-square test or Fisher's exact test based on the frequency and percentage of all recorded adverse events between two groups.

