#### Suspension criteria

2.3.3.

(1)The condition deteriorates, or more serious complications occur.(2)Serious adverse reactions occurred.

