#### Dropout criteria

2.3.4.

(1)Participants do not follow the original treatment plan (poor compliance).(2)Participants receive other treatments without investigator's permission during the intervention period.(3)Participants withdrew from the trial due to their own factors.

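### With outcomes measured only at baseline and week 4, LOCF scores every missing participant as unchanged, which shrinks the ITT effect under equal dropout and can distort it either way under unequal dropout

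*Protocol article*

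**What the plan says.** Statistical analysis (2.9) commits to both ITT and per-protocol analyses and fixes the missing-data rule for the first: "The Last Observation Carried Forward Analysis (LOCF) rule will be applied for missing data in ITT analysis". Data collection and management (2.8) gives the schedule: "The primary and secondary outcomes will be assessed at baseline and 4 weeks (at the end of the intervention". The Abstract agrees, and no intermediate outcome visit is described.

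Two further lists bear on who might be missing. Dropout criteria (2.3.4) include "Participants do not follow the original treatment plan (poor compliance", together with unpermitted other treatment and the participant's own withdrawal. Suspension criteria (2.3.3) are separate and include "The condition deteriorates, or more serious complications occur". Neither list says whether these participants are still assessed at week 4.

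Sample size calculation (2.6) uses "With the test levels set at *α* = 0.05 (2-sided), *β* = 0.1", a difference taken from "the maximum acceptable right/left reach distance difference was 4 cm", and a spread from a pre-experimental observation: "The standard deviation of the comprehensive score of Y-Balance test in the pre-experimental observation was 4.95". It reports "It is substituted into the sample size calculation formula, *n* = 32.15" and raises this to 36 per group for 10% dropout, 72 in total.

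**The concern.** LOCF presumes a series of post-baseline measurements from which the latest can be taken. Here there is one post-baseline measurement. If it is missing, only the baseline score is left, so the rule is baseline carried forward under another name. It asserts that every missing participant neither improved nor worsened.

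The protocol's own account makes that implausible. The Background says functional training can enhance ankle stability and improve balance, and both arms receive it. A missing control participant is therefore denied an expected gain, a missing Tuina participant is denied a possibly larger one, and a missing participant who got worse is lifted back to baseline.

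Three things are at stake. The ITT estimate is biased whenever missing participants truly changed. The direction depends on which arm loses more people, and equal loss cannot be presumed: participants and doctors are unblinded (2.7), and only one arm adds about 30 minutes of Tuina per session (2.4.2). Finally, the step to 36 per group treats dropouts as removed from the analysis, whereas 2.9 keeps them in it with zero change.

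**Working it through.** **Inputs from the document (2.6):** two-sided α = 0.05, β = 0.1, difference Δ = 4, SD = 4.95, 10% dropout, 36 per arm. The difference is a right/left reach distance in cm and the SD belongs to the composite score, which 2.5.1.1 expresses in per cent. That mismatch is a separate matter; the inputs are taken at face value here.

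**Assumed, not in the document:** control-arm gain g (0 to 8 points), unequal dropout splits, baseline to week-4 correlation (0.5 to 0.7), and missingness unrelated to outcome.

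**Step 1: reproduce the plan's figure.** n = 2(z₀.₉₇₅ + z₀.₉₀)²SD²/Δ² = 2 × (1.96 + 1.28)² × 4.95² / 4² = 32.15. Then 32.15/0.9 = 35.7, rounded up to 36. The figure reproduces. With the lost cases left out, 36 × 0.9 = 32.4 per arm are analysed: SE = 4.95√(2/32.4) = 1.230, and power = Φ(4/1.230 − 1.96) = 90.2%.

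**Step 2: what LOCF estimates.** With missing fractions d_T (Tuina) and d_C (control), and zero change for missing cases, the expected difference is

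D = (1 − d_T)(g + Δ) − (1 − d_C)g.

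With equal dropout d this is (1 − d)Δ, so at 10% it is 0.9 × 4 = 3.6.

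**Step 3: power of the unadjusted comparison, equal dropout.** With 36 per arm, SE = 4.95√(2/36) = 1.167.

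| Missing per arm | D | Power (normal approximation) |
|---|---|---|
| 5% | 3.8 | 90.3% |
| 6% | 3.76 | 89.7% |
| 10% | 3.6 | 87.0% |
| 15% | 3.4 | 83.0% |
| 20% | 3.2 | 78.3% |

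At 10% the t-test gives 86.1%. About 40 analysed per arm would be needed for 90% power at 3.6.

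**Step 4: added variance.** Mixing changed and unchanged participants adds d(1 − d) × (mean change)² to each arm's variance. At 10% missing and g = 4:
- Tuina: 24.50 + 0.09 × 8² = 30.26
- Control: 24.50 + 0.09 × 4² = 25.94
- SE = √((30.26 + 25.94)/36) = 1.249
- Power = Φ(3.6/1.249 − 1.96) = 82%

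Over g = 0 to 8 this runs from 86.0% to 74.7%.

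**Step 5: simulation, changing one thing at a time** (36 per arm, g = 4, correlation 0.6, 10% missing per arm).

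| Test | LOCF | Observed data only |
|---|---|---|
| t-test on week-4 score | 81% | 89% |
| ANCOVA | 94% | 97–98% |

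LOCF costs about 8 points of power with the t-test and about 4 with ANCOVA.

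**Step 6: unequal dropout** (assumed splits).

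| True effect | g | Missing control / Tuina | D under LOCF | Rejection rate, t-test |
|---|---|---|---|---|
| 4 | 4 | 5% / 20% | 0.80 × 8 − 0.95 × 4 = 2.6 | about 52% |
| 0 | 4 | 20% / 5% | 0.95 × 4 − 0.80 × 4 = +0.6 | about 8% |
| 0 | 8 | 20% / 5% | 0.95 × 8 − 0.80 × 8 = +1.2 | about 14% |

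ANCOVA on the LOCF data gave the same biases. In the two no-effect rows its type I error was higher, about 10% and 19%. ANCOVA on observed data was unbiased, with type I error of 5.1% to 5.5%.

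**The case against.** The other side has several good points.

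- **Who goes unmeasured.** A reader might infer that the dropout rules turn non-adherent and deteriorating participants into baseline-carried cases, and so contradict ITT. The document does not support this. Deterioration is a suspension criterion (2.3.3), not a dropout criterion (2.3.4). Nothing says that either group misses week 4. LOCF applies only to missing data, and 2.8 states the week-4 assessment without exception. The dropout categories could simply define per-protocol exclusions. Follow-up after stopping treatment may also be set out in the full protocol, which is not shown.
- **Power.** A reader might infer that power must fall below 90%. That holds for the unadjusted comparison that 2.6 sized, once dropout exceeds about 5% to 6%. Section 2.9 does not fix the primary test and allows covariance adjustment. ANCOVA on LOCF data gave about 94%. A change-score analysis at an assumed correlation of 0.7 gave 98%, 95% and 87% for control gains of 0, 4 and 8.
- **Size of the gain from repair.** Setting 81% (t-test, LOCF) against 97% (ANCOVA, observed data) would credit the missing-data rule with a benefit that comes partly from baseline adjustment.
- **Type I error.** With 10% missing in each arm the bias is conservative and type I error stays nominal (4.6% to 4.7%). The inflated figures need unequal splits, for which the document gives no figures.
- **The remedy.** Observed-data ANCOVA was unbiased because missingness was simulated as unrelated to outcome. This does not show that it copes with participants who leave because they are worse.

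All of these stand as limits on the claim. None makes zero change a sound value for a missing participant: covariance adjustment leaves the bias in place, and a parallel per-protocol analysis does not repair the ITT estimate.

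**Conclusion.** The point holds in a bounded form. With two measurement times, the stated LOCF rule always inserts the pre-treatment score and biases the ITT estimate whenever missing participants truly changed. This is a rule the article fixes, not a detail left to another document.

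At the planned 10% dropout, equal in both arms, the attenuation is 10% (4.0 to 3.6). Power of the unadjusted comparison is about 87% on the plan's inputs, and about 81% with an assumed control gain of 4 points, against 89% to 90% for the same comparison on observed data. Unequal dropout can hide or create an effect, and the figures for it rest on assumed splits and gains.

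For participants who meet the dropout or suspension criteria the conclusion is conditional. If they are not assessed at week 4, LOCF scores them as unchanged, including those who deteriorated. If they are assessed, LOCF does not touch them.

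**What to change.** 1. In 2.9, replace LOCF for the ITT analysis with ANCOVA of observed week-4 scores adjusted for baseline, or with multiple imputation by arm using baseline scores and sessions attended.
2. Add a sensitivity analysis that gives worse-than-baseline values to participants suspended for deterioration and missing at week 4. The main analysis is unbiased only if missingness is unrelated to outcome given the modelled variables.
3. State in 2.3.3, 2.3.4 and 2.8 that participants who meet the suspension or dropout criteria and still consent keep the already scheduled week-4 assessment and enter ITT with their observed values. This concerns measurement only, not their treatment.

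The cost is a wording change, a short amendment, slightly more analysis work and some follow-up calls. No new visit is needed. The third item should come first, because a missed week-4 assessment cannot be recovered later.
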